
### Procedures and interventions

In Part 1, patients undergo ctDNA MRD testing (CancerDetect™, IMBdx Inc.) using 20 mL whole-blood sample collected 3–6 weeks after surgery [10, 14–16]. Whole-exome sequencing (WES) of the surgical tumor tissue and matched white blood cells is first performed to identify patient-specific somatic mutations. Based on these findings, a personalized target capture panel comprising up to 100 variants is designed. ctDNA MRD testing is then conducted by high-depth sequencing of postoperative plasma DNA using this customized panel.

All enrolled patients initially receive 3 months of standard chemotherapy (FOLFOX/CAPOX). MRD test results will be disclosed to investigators and study participants within 3 months of initiating chemotherapy. For MRD-negative patients identified after completing the initial 3 months of standard chemotherapy, the decision to continue with an additional 3 months of chemotherapy (to complete a 6-month course) or to stop after 3 months will be left to the investigator’s discretion. MRD-positive patients will be screened for participation in Part 2 of the study after completion of the 3 months of chemotherapy. A total of 236 MRD-positive patients will be randomized 1:1 to receive either intensified chemotherapy (3 months of mFOLFIRINOX) or continued standard chemotherapy (an additional 3 months of FOLFOX or CAPOX).

The mFOLFIRINOX regimen consists of oxaliplatin (85 mg/m^2^), leucovorin (400 mg/m^2^), irinotecan (150 mg/m^2^), and 5-fluorouracil (2,400 mg/m^2^ for 46 h as a continuous infusion). The first dose of the clinical trial treatment is recommended to be administered on the scheduled start date of the next cycle of adjuvant chemotherapy—cycle 7 for FOLFOX or cycle 5 for CAPOX—and must be given within 3 weeks following randomization. Administration within + 7 days from Day 1 of each treatment cycle is permitted.

Stratified randomization was employed using mixed block sizes of 2 and 4 within each stratum. Patients are assigned through the web-based clinical trial platform system called Mytrial. The stratification factors were:•Risk group: high-risk (stage III colon cancer with T4 and/or N2) vs. low-risk (stage III without T4/N2 or stage II colon cancer)•Adjuvant chemotherapy regimen: FOLFOX vs. CAPOX•Study site

For patients enrolled in Part 2, recurrence surveillance will be performed every 12 ± 4 weeks during the first 2 years following randomization, and every 24 ± 4 weeks during the third year. Surveillance will include carcinoembryonic antigen (CEA) testing, contrast-enhanced abdominal/pelvic CT, chest CT, and serial ctDNA MRD assessment using 20 mL whole-blood samples (Part 2, Fig. 3).

**Fig. 3 Fig3:**
[figure not shown]
Recurrence surveillance protocol in the Part 2 study

MRD-negative patients, as well as MRD-positive patients who are ineligible for or decline participation in Part 2, will remain in the Part 1 observational study and undergo routine surveillance. In this group, recurrence monitoring will be conducted every 24 ± 4 weeks for a total of 3 years and will include CEA testing, contrast-enhanced abdominal/pelvic CT, and chest imaging with either CT or X-ray (Fig. 4).

**Fig. 4 Fig4:**
[figure not shown]
Recurrence surveillance protocol in the Part 1 study

For both group groups, if recurrence is confirmed during surveillance—or if a patient receives other treatments or participates in another clinical trial that may impact this study—recurrence surveillance will be discontinued.

After completion of the 3-year recurrence surveillance period, all patients will enter long-term follow-up and be monitored for survival every 6 months until death or the end of the study.

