## Methods

### Study aim and design

This multi-center, prospective, open-label, platform trial consists of two sequential parts: a prospective observational study (Part 1) and a randomized controlled phase III clinical trial (Part 2) (Fig. 1). Part 1 involves screening approximately 1,200 patients for MRD using postoperative ctDNA analysis, while Part 2 evaluates the efficacy of intensified chemotherapy (3 months of FOLFOX or CAPOX followed by 3 months of mFOLFIRINOX) versus standard chemotherapy (6 months of FOLFOX or CAPOX) in MRD-positive patients identified in Part 1 (Fig. 2).

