### Study endpoints

The primary endpoint of the Part 1 observational study is the proportion of patients who proceed to enrollment in the Part 2 interventional trial. Secondary endpoints include the rate of postoperative ctDNA MRD positivity, recurrence rates stratified by ctDNA MRD status, and recurrence rates according to digital pathology findings.

The primary endpoint of the Part 2 randomized trial is the 3-year DFS, defined as the time from the date of randomization to the date of first documented disease recurrence or death from any cause, whichever occurs first, with censoring at 3 years. The occurrence of second primary cancers will not be considered an event.

Secondary endpoints include 5-year overall survival (OS), defined as the time from the date of randomization to the date of death from any cause, with censoring at 5 years; 5-year DFS; treatment-related adverse events based on NCI-CTCAE v5.0; treatment compliance; and patient-reported outcomes, assessed using the EORTC QLQ-C30 questionnaire. Additionally, ctDNA dynamics—including clearance rate—will be assessed as exploratory endpoints.

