### Statistical analysis

A total sample size of 236 patients (118 per arm) of the Part 2 study was calculated based on an assumed hazard ratio (HR) of 0.64 for 3-year DFS, providing 80% power with a two-sided alpha of 0.05, and accounting for a 10% dropout rate. This HR corresponds to an estimated 3-year DFS rate of 46.3% in the experimental arm and 30.0% in the control arm, reflecting a clinically meaningful and statistically significant absolute improvement of 16%.

Assuming uniform accrual over 3 years and a minimum follow-up of 3 years for the last enrolled patient, a total of 159 DFS events is required. One interim efficacy analysis is planned after 30% of events have occurred. Sample size estimation was performed using the rpact package in R (version 4.1.1).

Survival outcomes (DFS and OS) will be analyzed using the Kaplan–Meier method and compared between treatment groups using the stratified log-rank test, with stratification factors identical to those used at randomization. Treatment effects will be estimated using a stratified Cox proportional hazards model to calculate the HR and its corresponding two-sided 95% confidence interval (CI).

Efficacy analyses for Part 2 will be performed primarily using the Full Analysis Set (FAS), defined as a modified intention-to-treat (mITT) population that includes all randomized patients who have received at least one dose of the investigational product, in accordance with the ITT principle. Patients will be excluded from the FAS if they (1) do not meet key eligibility criteria, (2) have not received any investigational product, or (3) have not undergone at least one post-randomization assessment.

Sensitivity analyses will be conducted on the Per Protocol Set, a subset of the FAS that includes patients who adhere to the protocol. Safety analyses will be based on the Safety Set, defined as all patients who received at least one dose of the investigational product.

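### Part 2 stops looking for recurrence once a patient gets other treatment or joins another trial, which puts the primary DFS endpoint at risk of informative loss

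*Protocol article*

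**What the plan says.** All references are to the protocol article.

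- **Stopping rule** (Procedures and interventions, text after Fig. 4). Besides confirmed recurrence, surveillance ends "if a patient receives other treatments or participates in another clinical trial that may impact this study—recurrence surveillance will be discontinued". The sentence is written for both follow-up groups, so it covers the randomized patients.
- **Primary endpoint** (Study endpoints). Part 2 DFS is "defined as the time from the date of randomization to the date of first documented disease recurrence or death from any cause". The only censoring that the definition names is administrative, at 3 years. New therapy or entry to another trial is neither an event nor a stated reason for censoring.
- **Analysis population** (Statistical analysis). The Full Analysis Set is a modified ITT set of "all randomized patients who have received at least one dose of the investigational product, in accordance with the ITT principle".
- **Surveillance content** (Procedures and interventions). Part 2 patients have CEA, CT and "serial ctDNA MRD assessment using 20 mL whole-blood samples" every 12 ± 4 weeks for two years and every 24 ± 4 weeks in the third.
- **Blinding** (Study aim and design). "This multi-center, prospective, open-label, platform trial consists of two sequential parts".
- **Survival follow-up** (text after Fig. 4). Once the 3 years of surveillance are over, "all patients will enter long-term follow-up and be monitored for survival every 6 months until death or the end of the study".

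**The concern.** The endpoint counts recurrence up to 3 years whatever the patient receives in the meantime. The follow-up rule stops the search for recurrence at an event that happens after randomization and is not a DFS event. A recurrence after that point is missed, picked up by chance in routine care, or seen only later as a death.

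The decision to give other treatment without confirmed recurrence may be related to prognosis. Treating staff know the arm, every Part 2 patient is known to be MRD-positive, and CEA and CT results come in regularly. A rising marker or an equivocal scan could plausibly prompt such a decision. If these patients were then treated as event-free at their last assessment, Kaplan–Meier DFS would be too high. If the exits differed between arms, the hazard ratio would shift as well, and neither the stratified log-rank test nor the Cox model would correct it.

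**Working it through.** **1. The plan's own figures reproduce.** Inputs from Statistical analysis: HR 0.64, two-sided alpha 0.05, 80% power, 3-year DFS of 30.0% and 46.3%, 3 years of accrual plus at least 3 years of follow-up, 10% dropout.

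- 0.30^0.64 = 0.463, as stated.
- Schoenfeld events: 4(1.960 + 0.842)² / (ln 0.64)² = 158, against 159 stated.
- Exponential DFS with the stated accrual and follow-up gives a mean event probability of 0.751. 159/0.751 = 212 evaluable patients, and 212/0.90 = 236.

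These figures are not in dispute. They supply the inputs below.

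**2. Illustration of the stopping rule.** The documents give no rate of exit, so the shares are assumptions. Let f0 (control) and f1 (experimental) be the share of DFS events pre-empted by an exit, with the patient censored at that time and nothing recovered later.

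- Hazards: control −ln(0.30)/3 = 0.4013 per year; experimental 0.64 × 0.4013 = 0.2569.
- Observed HR = 0.64 × (1 − f1)/(1 − f0).
- Observed 3-year DFS = 0.300^(1 − f0) and 0.463^(1 − f1).
- Events by 3 years among 212 patients (106 per arm) = 106 × [(1 − f0) × 0.700 + (1 − f1) × 0.537].

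| f0 / f1 | Observed HR | 3-year DFS, control / experimental | Events |
|---|---|---|---|
| 0 / 0 | 0.64 | 30% / 46% | 131 |
| 10% / 10% | 0.64 | 34% / 50% | 118 |
| 15% / 5% | 0.64 × 0.95/0.85 = 0.72 | 36% / 48% | 117 |
| 5% / 15% | 0.64 × 0.85/0.95 = 0.57 | 32% / 52% | 119 |

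Equal loss of 10% costs 131 − 118 = 13 events.

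**3. Check with a different mechanism.** A large simulation censored a share of the patients due to recur within 3 years, 3 months before recurrence (236 patients, 3-year cap, no other dropout).

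- 10% in both arms: HR 0.64, control DFS 33.6%, events down from 146 to 131.
- 10% or 20% in control only: HR 0.70 or 0.79.
- 10% or 20% in experimental only: HR 0.58 or 0.52.

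The pattern is the same: equal loss inflates DFS and costs events, and only unequal loss moves the HR.

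**4. Why these are upper bounds.** Both calculations remove the event for good. In practice a later death within 3 years would still count, and so could a recurrence documented in routine care.

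**The case against.** The strongest reply is that the rule ends scheduled surveillance and says nothing about analysis. A reader might infer that these patients are censored at exit and that the primary DFS is therefore biased. The documents do not say so: the only censoring named is at 3 years, and the handling of new therapy may be in the statistical analysis plan, which is not shown. Deaths also remain obtainable through survival follow-up.

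A reader might also infer that those who leave are the patients closest to relapse, driven by rising ctDNA. That is plausible but not stated. The disclosure described under Procedures and interventions is of MRD results within 3 months of starting chemotherapy, which concerns the postoperative test. Nothing says that serial Part 2 ctDNA results are returned or acted on, and ctDNA dynamics are an exploratory endpoint. CEA and CT are enough to make informative exit possible, but not to show that it happens.

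The shares are assumed, and no passage suggests that the arms differ or in which direction. The rule is limited to treatments or trials that could affect the study, and the 10% dropout allowance may absorb some loss of events, though not bias. Nor should the gap between the 131 events in the first row of the table and the 159 required be charged to this rule. It comes from capping DFS at 3 years and is a separate matter.

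All of this stands and limits the claim to a risk of unknown size. It does not remove the point. The rule governs data collection and is stated outright, and an analysis plan can choose a censoring rule but cannot restore assessments that were not made.

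**Conclusion.** The concern holds as a risk, not as a demonstrated bias. The stopping rule does not fit the DFS definition or the ITT principle, and following it can lose the recurrence component of the primary endpoint for a reason that may be related to prognosis.

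The size cannot be derived from the documents. Under the assumed shares, and as upper bounds, equal loss of 10% leaves the HR at about 0.64, raises apparent control 3-year DFS from 30% to about 34%, and costs about 13 events. Loss of 15% against 5% gives an observed HR of about 0.72 if control loses more and about 0.57 if the experimental arm does. The direction is unknown. The figures rest on exponential DFS at the planned rates, 212 evaluable patients and no later recovery of events. Severity: should fix.

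**What to change.** For Part 2, separate the end of recurrence ascertainment from the start of other treatment:

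- Continue the scheduled recurrence assessments, or collect recurrence dates from routine or other-trial scans, until recurrence, death, withdrawal of consent or the end of the 3-year DFS period, regardless of other treatment or trial entry.
- Count these events in the primary analysis (a treatment-policy approach).
- Record the date and reason of any new therapy or trial entry, by arm.
- Use censoring at new therapy only as a sensitivity analysis.

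The cost is mainly protocol and case report form wording, since the assessments are already scheduled. There are two small downsides. Assessment intervals may differ for patients in another trial. For patients already taken off surveillance, recurrence data would have to be retrieved retrospectively where consent allows. The Discussion puts the study start at December 2022 and Part 2 enrolment at 116 of 236 in April 2025. That is 28 months, so at that date no patient had completed 3 years and 236 − 116 = 120 were still to be enrolled. Most of the follow-up could still be protected.

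### 5-year DFS is a Part 2 secondary endpoint, but recurrence is not systematically ascertained after year 3, so it would be either biased upward or not estimable

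*Protocol article*

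**What the plan says.** Study endpoints defines DFS for Part 2 as time from randomization to the "date of first documented disease recurrence or death from any cause, whichever occurs first, with censoring at 3 years". Among the secondary endpoints it gives OS and then 5-year DFS: "with censoring at 5 years; 5-year DFS; treatment-related adverse events based on NCI-CTCAE v5.0". The censoring phrase at the start of that quote belongs to OS. No separate event or censoring rule is given for 5-year DFS.

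Procedures and interventions schedules Part 2 surveillance (CEA, abdominal/pelvic CT, chest CT and ctDNA) "every 12 ± 4 weeks during the first 2 years following randomization, and every 24 ± 4 weeks during the third year". Nothing is scheduled beyond that. The same section, in the text after Fig. 4, then says that once the three years of recurrence surveillance are over, "all patients will enter long-term follow-up and be monitored for survival every 6 months until death or the end of the study". No imaging, CEA or recurrence assessment is named for this phase.

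**The concern.** An endpoint that counts documented recurrence is to be reported at year 5, while the described collection of recurrence data stops at year 3. Deaths in years 3 to 5 are collected; recurrences in those years have no stated route into the data.

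A patient who relapses in year 4 and is alive at year 5 may therefore be counted as disease-free. One who relapses in year 4 and dies before year 5 may enter with the date of death instead of the date of relapse. At stake is whether the trial can report a 5-year DFS in either arm that means what its definition says.

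**Working it through.** **1. The plan's own figures.** Statistical analysis gives an "assumed hazard ratio (HR) of 0.64 for 3-year DFS", with 3-year DFS of 30.0% (control) and 46.3% (experimental). Under proportional hazards 0.30^0.64 = 0.463, so these agree. The implied constant hazards are −ln(0.30)/3 = 0.4013 per year and 0.64 × 0.4013 = 0.2568 per year. No stated number is wrong on this point.

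**2. Two possible censoring rules.** The article does not choose between them.
- *At risk to last survival contact.* An unrecorded late relapse in a living patient counts as disease-free time, and one known only through death is dated late. The Kaplan–Meier estimate at year 5 is too high.
- *Censored at last recurrence assessment.* Almost every event-free patient leaves the risk set near year 3. Hardly anyone is at risk between years 3 and 5, and 5-year DFS is essentially not estimable.

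**3. Size under the first rule.** The documents give no hazard after year 3. Assume 0.05 to 0.20 per year in control and keep the hazard ratio at 0.64, so 0.032 to 0.128 per year in the experimental arm. Then S(5) = S(3) × exp(−2h):

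| Arm | Late hazard h | True 5-year DFS | Ceiling if no late event is captured | Gap (points) |
|---|---|---|---|---|
| Control | 0.05 | 0.300 × exp(−0.10) = 27.1% | 30.0% | 2.9 |
| Control | 0.20 | 0.300 × exp(−0.40) = 20.1% | 30.0% | 9.9 |
| Experimental | 0.032 | 0.463 × exp(−0.064) = 43.4% | 46.3% | 2.9 |
| Experimental | 0.128 | 0.463 × exp(−0.256) = 35.8% | 46.3% | 10.5 |

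The gaps are upper bounds for each assumed hazard, because they suppose that no late recurrence is learned of and nobody dies in the two years.

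**4. Other late hazards.** If the planning hazards simply continued, 5-year DFS would be exp(−5 × 0.4013) = 13.4% and exp(−5 × 0.2568) = 27.7%. That puts 16.6 and 18.6 points, or about 20 and 22 first events per 118 patients, in the unsurveilled period. If the hazard fell to 50%, 25% or 10% of its earlier level, the fall in years 3 to 5 would be about 10, 5.5 or 2.3 points per arm.

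**5. Partial capture through death.** Suppose late recurrences enter only when the patient dies, with an assumed median of 1 to 3 years from recurrence to death (m = ln 2/median). The fraction of year-3 survivors captured by year 5 is (1 − e^(−2h)) − h(e^(−2h) − e^(−2m))/(m − h). Example: control, continuing hazard h = 0.4013, median 1 year (m = 0.693). This gives 0.552 − 0.272 = 0.279, which is 51% of the 0.552 who relapse. Across both arms and medians of 1 to 3 years the captured share is about 21 to 51%. Apparent 5-year DFS is then about 22 to 26% against a true 13.4% (control), and 37 to 42% against 27.7% (experimental): still too high, but by less than with no capture.

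**The case against.** Much of the case against a stronger claim stands.

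- A reader might infer that every recurrence after year 3 is lost. The documents do not support that. Death from any cause is a DFS event, so late relapses that end in death by year 5 do count, though late-dated. The event is a documented recurrence, not one found at a scheduled trial scan, so a relapse diagnosed in routine care and mentioned at a 6-monthly contact would qualify. No sentence says that such information is ignored.
- A reader might also infer that 5-year DFS is certain to be overstated. That follows under one censoring rule only, and the rule may be in the statistical analysis plan, which is not shown.
- The word survival is not used only for vital status in this document: "Survival outcomes (DFS and OS) will be analyzed using the Kaplan–Meier method". Still, the follow-up sentence sets survival monitoring against a recurrence surveillance period that has ended, and runs it until death. Vital status is the natural reading, and sites would follow it.
- The treatment contrast may hardly move. With the hazard ratio maintained, the true 5-year difference is 43.4 − 27.1 = 16.3 to 35.8 − 20.1 = 15.7 points, against 16.3 if nothing is captured. This depends on the assumption: with the same late hazard of 0.20 in both arms, the experimental arm would be at 0.463 × exp(−0.40) = 31.0% and the true difference would be 10.9 points.
- It is tempting to add that the plan manufactures an apparent cure plateau. The article makes no such claim, and none should be attributed to it.

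What each contact records is often left to the full protocol. Here, though, the article does describe the post-year-3 phase, and its description does not support the endpoint it lists.

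**Conclusion.** The mismatch is in the text and holds under either censoring rule. Followed as written, the plan yields a 5-year DFS that is biased upward or that cannot be estimated much beyond year 3. Under the first rule the overstatement is at most about 3 to 10 points per arm. That range rests on an assumed control hazard of 0.05 to 0.20 per year after year 3, the hazard ratio of 0.64 carried forward, and no late event captured. Deaths and incidentally learned relapses would shrink it; a late hazard closer to the planning hazard would enlarge it.

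The point concerns one secondary endpoint. The primary endpoint is censored at 3 years, which scheduled surveillance covers, and is not affected as defined. It should be put right, but it does not threaten the main conclusion.

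**What to change.** Reconcile Study endpoints with the surveillance and long-term follow-up text in Procedures and interventions, in one of two ways.

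1. Keep 5-year DFS. At each planned 6-monthly contact up to year 5, record recurrence status, date and site from routine care, and the date when recurrence was last assessed. State that these recurrences are events for 5-year DFS and that the date of last recurrence assessment is used for censoring.
2. Otherwise, remove 5-year DFS from the secondary endpoints.

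The first option costs a few case report form fields at contacts already planned, with no added scans. Its downside is small: late recurrences would come from non-uniform routine imaging, so their dates will be less exact than those in years 1 to 3, and the report should say so. Early action helps. According to the Discussion the study has run since December 2022, with 116 of 236 Part 2 patients enrolled by April 2025. Late relapse dates are harder to recover in retrospect, so the fields should be in place before the earliest randomized patients finish year 3.
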